### Inclusion/exclusion criteria

The NTDP and WHO recommendations for the treatment of endemic communities and monitoring and evaluation of treatment programmes, target all individuals aged 5 years and above. As such, the same population will be used in this study. Only healthy volunteers, both men and women will be recruited into the study. The following inclusion and exclusion criteria will apply in the selection of study participants:

#### Inclusion criteria

Criteria for eligibility to participate in the human study:All study participants must be resident in the disease endemic community for at least 12 monthsAll study participants must be willing to provide informed consent/assentAll study participants must be willing to donate blood (per the protocol)For mosquito collectors only: volunteers over the age of 18 years who have received formal training in safe and scientifically reliable mosquito collection

#### Exclusion criteria

The following individuals are ineligible to participate in the study:Individuals who are recent residents (less than 12 months) in the study districts.Individuals who are unable to give informed consent due to illness, serious medical problems or refusal to participate in the studyPregnant women – determined through questioning or visual examination at the time of consentChildren below the age of 5 years

### Data management and analysis

Field and laboratory data will be recorded by technicians using Samsung Galaxy Tabs A7.0., and entered into a customised database. All data collections tools are coded using CSPro and the data will be transferred onto a secured server.

The analysis will be aimed at (1) assessment of any differences in baseline characteristics between treatment groups, (2) intent-to-treat analysis, i.e. assessment of the effectiveness of the single or twice-yearly treatment regimens on infection intensities and disease outcome and (3) assessment of differences in adherence to the treatment regimens between the groups, potential confounding, and adjusted effectiveness analysis.

All statistical analyses will be based on the clusters with both baseline and endpoint parasitological results. Results will be presented as appropriate effects sizes with a measure of precision (95% CIs). Unadjusted and adjusted results will be presented for all analyses. Covariates in adjusted analyses will be predefined and will include participation in previous MDAs and access and use of bed nets. For continuous outcomes, analyses will adjust for baseline by inclusion of the cluster mean of the outcome in question as a covariate in statistical models.

Demographic and population characteristics of clusters will be compared between study groups. These measures will be tabulated, but no significance tests will be performed to investigate for differences between groups at baseline. Statistical testing will be restricted to comparison between the two community-based treatment groups. Secondary outcomes will be pre-specified for statistical testing along with the primary outcome.

The summary statistic for each parasitological endpoint will be estimated, and compared using paired Student’s *t* tests. Changes in rate of infection will be expressed as percentage differences from the pre-treatment rates. The significance in differences in mosquito infection rates will be tested using the chi-square test. The significance of correlation between different indices will also be tested using the chi-square test. The significance of differences in monthly transmission potential before and after treatment will be tested with the non-parametric Mann-Whitney *U* test. Analysis of variance (ANOVA) will also be used in the intent-to-treat analysis for comparing the study groups. SPSS for WINDOWS 16 (SPSS Inc, Chicago, IL, USA) will be used for all statistical computations. The mf intensities will be adjusted for sampling time by multiplying the counts with a time-specific factor [38]. Geometric mean intensities (GMIs) of microfilaraemia and antigenaemia prevalence will be calculated [39].

Below is the statistical analysis strategy.

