## Background

Lymphatic filariasis (LF) is a debilitating, mosquito-borne, nematode infection that has been targeted for elimination as a public health problem by 2020. It affects 120 million people in 73 countries where 1.46 billion people are at risk of acquiring the infection through infectious mosquito bites. In 2000, the World Health Organisation, in collaboration with pharmaceutical companies and endemic country governments, launched the Global Programme to Eliminate LF (GPELF). Ivermectin (IVM) in combination with diethylcarbamazine (DEC) or albendazole (ALB) remain the drugs available for the large-scale control of LF [1]. These drugs only temporarily clear microfilariae (mf) without killing all adult worms [2], and it is assumed that a reduction in population mf load will lead to a simultaneous reduction, or even interruption, of transmission [3–5]. It is, therefore estimated, that five to six rounds of mass drug administration (MDA) are required to eliminate the disease. From 2000 to 2014, LF MDA included a cumulative total of 5.62 billion treatments delivered to more than one billion people at least once [6, 7]. Many countries including Ghana have since undertaken between 8 and 15 consecutive annual rounds of MDA in several implementation units without interrupting transmission. In Ghana, where the MDA coverage rates have been more than the required 65%, 29 sentinel sites with persistent residual infections have been identified, with microfilaria prevalence rates of above 1% [8]. Previous studies [9] revealed high prevalence of LF (13% antigen prevalence and 4.6% mf prevalence) in two communities in a district with persistent LF transmission. In these communities, individuals positive for LF were treated and followed at 3-month intervals for 1 year. The results showed a decline in prevalence after treatment, followed by an increase 6 months after treatment (Table 1).

**Table 1 Tab1:** Number of positives and parasite loads at different time points (Unpublished data – [name])

	Dec 2014 (pre treatment)	3 months post treatment	6 months Post treatment	9 months Post treatment	12 months Post treatment
ICT positives	48	17/48 (35.4%)	26/48 (54.2%)	23/33 (69.7%)	15/30 (50%)
mf positives	17/48 (35.4%)	4/48 (8.3%)	4/48 (8.3%)	3/33 (9.1%)	2/30 (6.7%)

*ICT i*mmunochromatographic test, *mf* microfilariae

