### Study population

This study will be undertaken in the Western Region of Ghana, which lies within the high rain forest vegetation climate zone of the West African subregion, with strands of mangroves. The highest mean temperature is 34 °C while the lowest is 20 °C. Relative humidity is very high, averaging between 75% to 85% in the rainy, and 70% to 80% in the dry seasons. Rainfall is experienced throughout the year with the highest monthly mean occurring around May and June (http://mofa.gov.gh/site/?page_id=1778). The main economic activities in the region are agriculture and fishing. The region has a commercial capital, Takoradi and an administrative capital, Sekondi, located about a 3.5-h drive away from Accra, the capital of Ghana. Besides the main administrative capitals, the communities in the districts are predominantly rural. The region is one of the highest endemic zones in the country [21].

The sites selected are areas that have had 13–15 rounds of yearly treatment, without interrupting transmission of LF. The study areas selected are also among the highest endemic communities (zones) in the country. Undertaking the study in these sites, therefore, provides the opportunity to assess the impacts of the intervention.

The study will be carried out in 18 clusters in the Western region of Ghana. Communities were selected following a review of the Neglected Tropical Disease Programme (NTDP) sentinel and spot check site monitoring data, as well as recommendation from the District Health Management Team (DHMT). Based on these, 18 communities were selected, distributed into three districts in the Western Region of Ghana (Fig. 3). In these districts, the persistent transmission of LF has been reported following several rounds of MDA [8] and previous studies also indicated inaccuracies in the treatment coverage data reported [22].

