### Sample size calculation

The sample size was calculated based on the null and alternative hypotheses, together with the type-I and type-II errors defined as follows:

Null hypothesis (H_0_): the additional dose of IVM is not more effective than the standard single dose per annum treatment (i.e. Treatment – Control = 0).

Alternative hypothesis (H_A_): the additional dose of IVM is more effective than the standard dose (i.e. Treatment − Control > 0).

The type-1 error rate (*α*), i.e. rejecting H_0_ when it is true, is set at 0.05, with a two-sided test. To control for type-II error (*β*), the probability of rejecting H_0_ when it is false is set at 0.80, taking into consideration budget allocation.

The hotspot districts have been receiving an annual single dose of IVM for the past 15 years with the prevalence rates ranging between 1% and 18.2%. Therefore, it is assumed that the new intervention would have an effect, expected to be larger than the effect of the standard control approach, with an effect size of 0.4. Based on these assumptions, the sample size was calculated using the Optimal Design software [34]. Thus, for 0.80 power the study requires a cluster size of 58.

With an expected non-response and a loss to follow-up of 37% (determined from previous unpublished studies), the sample size per cluster has been determined to be 80. With 18 clusters to be surveyed, a total of 1440 study participants, from the two study districts, will be expected to take part in this trial.

Study participants will not be paid as part of the survey. However, in order to mitigate the high dropout rates during follow-ups, participants will be compensated for the time lost for working during the days they are participating in survey activities, with an amount of 7 Cedis (equivalent to US$1.61). They will also be contacted at 14 days and 7 days prior to follow-up, in order to ensure their availability. Even though there is always the possibility of emergencies and other social responsibilities that may result in their unavailability, efforts will be made to reach them.

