#### Analysis strategy

Each of our study outcomes, i.e. prevalence and intensity of *W. bancrofti* mf, will be considered separately during the analysis. Loss to follow-up was taken into consideration during our sample size calculation. Therefore, regardless of the number of incomplete observations, we expect to end up with no less than 58 complete observations per community at the end of the study.

A panel of individual line plots for the study participants would be used in the assessment of within-person variability. Since the assumptions of likelihood are violated by the effect of within-group and within-subject clusters in longitudinal data, in assessing the transmission dynamics of LF infection, the measured covariates will be regressed separately on both the prevalence and the intensity of infections using a quasi-likelihood method, i.e. generalised estimating equations, which uses an association matrix instead of the diagonal matrix employed by the generalised linear models. As part of the model validation, the point-referenced residuals of the provisional models will be assessed for spatial autocorrelation. The results of this assessment would help to determine if unmeasured/unobserved factors in the study areas play relevant roles in the transmission dynamics of LF infections. Using classical geostatistical concepts, our final model would be adjusted for both the effects of the measured and unobserved factors.

For entomological endpoints, infection rates will be determined, using the polymerase chain reaction (PCR) [40] and LAMP [41] methods. The results will be analysed using the poolscreening software by Katholi and colleagues [42, 43].

The findings and data from this study will be used to develop a mechanistic model, which describes the variability in treatment responses in populations. This will be implemented into an already available and well-established transmission dynamic model for LF (LYMFASIM) [44, 45], which will then be used to systematically explore the consequence of twice-yearly treatment on the long-term impact of MDA and elimination prospects. LYMFASIM simulates the spread of *W. bancrofti* in a human community and the impact of control measures, with the advantage of accounting for a variety of parameters specific to the population of interest and output predictions [45, 46].

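### The chi-square test named for correlation between indices does not test correlation for quantitative indices or for any human-mosquito pair

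*Protocol article*

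**What the plan says.** The protocol article assigns tests to endpoints one after another in Data management and analysis. For mosquitoes: "The significance in differences in mosquito infection rates will be tested using the chi-square test". Directly after that: "The significance of correlation between different indices will also be tested using the chi-square test". Then: "The significance of differences in monthly transmission potential before and after treatment will be tested with the non-parametric Mann-Whitney" U test. The paragraph ends with: "Geometric mean intensities (GMIs) of microfilaraemia and antigenaemia prevalence will be calculated".

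No correlation coefficient is named anywhere. The article does not say which indices are to be paired, what the unit of analysis is, or how an index would be cut into categories. Study aims and objectives and the Discussion use the word indices for parasitological and entomological measures of transmission. The same analysis section also promises effect sizes with 95% confidence intervals and confines statistical testing to comparisons between the two treatment groups.

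**The concern.** The sentence is a positive choice of test, so it is not a detail left to an unseen analysis plan. For most of the indices listed, the choice does not fit the question. Geometric mean intensity and transmission potential are quantities, and a prevalence or mosquito infection rate is one proportion per community. People and mosquitoes share no individual unit that could be cross-classified, so a human and a mosquito index can be paired only by community or survey. The null hypothesis of interest is then no association across communities.

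A chi-square test can be applied to such data in only two ways. It can be run on counts, where its null is a different one. Or it can be run after splitting communities into high and low, for which no rule is given and which discards most of the information in at most 18 values. A statement that human and mosquito indices do or do not move together could then rest on a test of something else, or on one with little power. A chi-square P value also supplies no effect size or interval, which the section promises for its results.

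**Working it through.** The protocol gives no figure for this analysis, so there is nothing to reproduce. The check asks what each possible chi-square test responds to.

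**Inputs from the protocol article**
- Communities: "The study will be carried out in 18 clusters in the Western region of Ghana" (Study population).
- People per community: "we expect to end up with no less than 58 complete observations per community at the end of the study" (Analysis strategy), taken as stated.
- Human prevalence: 1% to 18.2% (Sample size calculation), drawn uniformly over that range.
- Type I error: "is set at 0.05, with a two-sided test" (Sample size calculation).

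**Assumptions not in the documents**
- Case A: the second index is a mosquito rate of 0.5% to 5%, with 100 units per community.
- Case B: the second index has the same range and sample size as the human index.
- Community rates are linked through a latent normal correlation of 0, 0.8 or 1.
- There were 3,000 runs per setting, so the Monte Carlo standard error is at most √(0.5 × 0.5 / 3,000) = 0.9 percentage points.

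**Share of runs significant at 5% (case A / case B)**

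| Test | Correlation 0 | Correlation 0.8 | Correlation 1 |
|---|---|---|---|
| Chi-square, pooled proportions | 100% / 21% | 100% / 9% | 100% / 5% |
| Chi-square, positives by community (2 × 18) | 65% / 88% | 13% / 16% | 2.7% / 1.8% |
| Chi-square after median split (2 × 2) | 4.8% / 4.5% | 21% / 31% | 34% / 53% |
| Pearson | 5.4% / 4.1% | 36% / 60% | 61% / 87% |
| Spearman | 5.4% / 4.6% | 39% / 62% | 63% / 88% |

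**Reading the table**
1. The pooled test asks whether two overall rates are equal. When they differ (case A) it is always significant, whatever the correlation. When they have the same range (case B) it rejects less often as correlation rises.
2. The 2 × 18 test asks whether positives are spread over communities in the same way for both indices. It also runs backwards as a test of correlation.
3. The median split has valid size but loses power. Its power relative to Spearman is 20.8/38.7 = 0.54 (A) and 30.9/61.5 = 0.50 (B) at correlation 0.8, and 34.0/63.2 = 0.54 (A) and 52.8/88.3 = 0.60 (B) at correlation 1. With nine communities on each side, every expected cell count is 9 × 9 / 18 = 4.5.
4. A second set of assumptions (80 people per community, between-village coefficient of variation 0.6) gives similar ratios. With mean rates of 13% and 4.6% they are 30/60 = 0.50 at latent correlation 0.8 and 45/81 = 0.56 at 0.95. With both means at 10% they are 38/73 = 0.52 and 55/90 = 0.61.

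**Where chi-square is right**

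For two binary markers in the same n persons, chi-square = n × φ², where φ is their correlation coefficient. In one simulated set of 1,440 people both sides equal 137.26. With independent markers and unrelated village rates the test rejected in 5.9% of runs, close to nominal. For that kind of pair the test does address correlation.

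**The case against.** The strongest reply is that the sentence names neither the indices nor the unit, and that Survey procedures provides several binary markers on the same person: antigen, microfilariae and the Wb123 antibody. For such a pair chi-square is a legitimate test of association, as shown above. This stands. A reader might infer that chi-square never tests correlation, and that is too absolute. But the sentence is not confined to such pairs, and this reading cannot cover intensity, transmission potential or any human-mosquito link.

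A second reply concerns size. A reader might infer from the pooled-count row that the plan will almost certainly declare links between unrelated indices. The article does not support that. It does not say that pooled counts will be compared, and the median-split version has valid size.

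Nor can the Background figures, "high prevalence of LF (13% antigen prevalence and 4.6% mf prevalence) in two communities", serve as an example of two unrelated indices. Under Survey procedures only antigen-positive people are followed up for night blood, so microfilaria-positives are a subset of antigen-positives. The article's numbers fit that: 4.6/13 = 35.4%, and Table 1 has 17/48 = 35.4% before treatment. This also limits the remedy. In a simulation of such nesting (18 villages, 80 people each), with the microfilaria share independent of village prevalence and its coefficient of variation set at 0, 0.3 or 0.6, Spearman on the two village counts was significant in 99.5%, 96% and 82% of runs. Rank correlation would declare that link largely by construction.

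Third, correlation between indices is not listed as an objective or outcome, transmission dynamics are assigned to generalised estimating equations, and testing is elsewhere limited to between-group comparisons. That limits the importance of the point. It does not correct the sentence.

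**Conclusion.** The point holds in limited form. For quantitative indices and for any human-mosquito pair, the named test either addresses a different null hypothesis or needs an unstated dichotomy that leaves roughly half to two thirds of the power of a rank correlation (0.50 to 0.61 in the settings tried). The direction held under both sets of assumptions. The exact percentages depend on assumed between-community variation, mosquito rates and mosquito sample sizes, which the article does not give.

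The simulations use all 18 communities for both indices. Entomologic surveillance says that vectors are collected in selected villages only, so power for human-mosquito pairs would be lower than shown if those are fewer than 18.

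A reader might infer that the trial's conclusion on transmission is at risk. The documents do not support that: this is a supporting analysis and does not affect the primary outcome, the between-arm comparison or the sample size.

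**What to change.** Replace the sentence in Data management and analysis with:

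*Association between quantitative indices will be estimated by Spearman's rank correlation with a 95% CI across the communities where both indices are measured. Association between two binary markers measured in the same persons will be tested with a chi-square or phi-type test that allows for clustering by village.*

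Add that the correlation of antigen and microfilaria counts will not be read as evidence of a link, because microfilariae are examined only in antigen-positive people in the surveys. Report microfilaria positivity among antigen-positives instead.

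The cost is a few lines of text. No new data are needed, and Spearman's coefficient is available in the software the article names. Reporting an estimate with an interval also fits the section's promise of effect sizes with 95% CIs.

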### Entomologic surveillance

Surveys for vectors and transmission of LF will be carried out quarterly throughout the first year, and subsequently every 6 months. Vector collection will be carried out in selected villages. To ensure that mosquitoes do not cross over between communities, vector collection communities will be at least 2 km apart.

In each community collections will be undertaken in 10 selected participants’ households, distributed so as to be representative of the community. The community will be divided into four approximate sections. All households in the section will be numbered. The day before the planned collection, the dice will be rolled to select the households. For example, if the dice is rolled and the number is 5, then the fifth house will be selected. Upon selection, the household head will be approached, the study explained and consent sought. If a household refuses participation or household members are absent, a different household will be selected as a replacement. Subsequently, the sum of the dice rolls will be added to the previous number, for the selection of the remaining households. At least two households will be selected per section.

Collections will be undertaken using the Pyrethrum Spray Collection (PSC) in the rooms provided by the consenting individuals. The PSC will be undertaken in the morning from 5 a.m. to 8 a.m. White bed sheets will be laid on the floor and other surfaces in the rooms, after mosquito hiding places (under the bed, tables) have been disturbed to displace any resting mosquitoes. The room will then be sprayed with pyrethrum insecticide (RAID insecticide), commonly found on the Ghanaian market) and left for about 15 min, after which the white sheets will be inspected for any dead or knocked down mosquitoes. The mosquitoes will be collected and placed in a petri-dish labelled with the village name, GPS coordinates and collection date. Collected mosquitoes will be identified using morphological identification keys [36, 37]. All mosquito collections will be undertaken by trained entomologists at the NMIMR.

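### The planned test of monthly transmission potential needs infective-larva data that the stated mosquito methods do not provide

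*Protocol article*

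**What the plan says.** Under Data management and analysis, the article commits to a named index and a named test: "The significance of differences in monthly transmission potential before and after treatment will be tested with the non-parametric Mann-Whitney" *U* test. The same paragraph separately plans a chi-square test of mosquito infection rates, so transmission potential is meant to be something other than the infection rate.

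The collection is described under Entomologic surveillance. On timing: "Surveys for vectors and transmission of LF will be carried out quarterly throughout the first year, and subsequently every 6 months". On method: "Collections will be undertaken using the Pyrethrum Spray Collection (PSC) in the rooms provided by the consenting individuals", and "The PSC will be undertaken in the morning from 5 a.m. to 8 a.m". On scale: "In each community collections will be undertaken in 10 selected participants’ households". On handling of the catch: "Collected mosquitoes will be identified using morphological identification keys".

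The laboratory read-out is under Analysis strategy, within Secondary outcomes: "For entomological endpoints, infection rates will be determined, using the polymerase chain reaction (PCR) [40] and LAMP [41] methods". The results then go to pool-screening software. Third-stage larvae (L3) are defined in the abbreviation list but appear nowhere in the body of the article.

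**The concern.** Transmission potential is a statement about infectivity: how many infective larvae a person is exposed to in a month. The stated read-out is a statement about infection: what share of mosquitoes carry parasite DNA. As described, a mosquito that has just taken in microfilariae with a blood meal can count as positive, although it is not infective.

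The first study objective covers entomological transmission indices, and the Background presents the effect on vectors as a gap left by earlier trials. If an index is built from DNA positivity and reported under the standard name, readers may take it as evidence about transmission that the stated data do not carry. Ingested microfilariae come from human blood, so such an index could also partly repeat the human microfilaria result rather than add independent evidence.

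**Working it through.** The article gives no figure for this index, so there is nothing to reproduce. The check is whether each component can be traced to a stated method.

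**Definition (assumed; the article gives none).** M = B × p × L, where B is bites per person in the month, p the proportion of mosquitoes infective, and L the mean L3 count per infective mosquito.

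**Components against stated methods**

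| Component | What the article describes | Obtained? |
|---|---|---|
| B | Spray catch of mosquitoes in rooms, early morning, 10 households per community | Indirectly at best. Fed mosquitoes per room occupant could stand in for indoor biting in a sampled month, but no such derivation is stated |
| p | PCR/LAMP infection rate, pool-screened | No. This estimates d, the share with parasite DNA; no stage-specific step is described |
| L | Morphological identification of the mosquitoes | No. No dissection or larval count is described |

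**Size of the gap.** Let f be the share of DNA-positive mosquitoes that carry L3, so p = f × d. Then M = (B × d) × (f × L). The stated methods could supply at most a proxy for B × d; the factor f × L is not observed. With assumed ranges f = 0.10 to 1.00 and L = 1 to 5:

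- lowest f × L = 0.10 × 1 = 0.1
- highest f × L = 1.00 × 5 = 5
- ratio = 5 / 0.1 = 50

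The same biting rate and the same infection rate therefore fit a 50-fold range of M. Using d in place of p sets f = 1. That can only overstate the infective proportion, by up to 1 / 0.10 = 10 times at the low end of the assumed range. For the whole index the direction is not fixed: B × d with no load term could be 10 times too high (f × L = 0.1) or 5 times too low (f × L = 5).

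**Consequence for the test.** Mann-Whitney uses ranks. If f × L were the same at every survey, ranking by B × d would equal ranking by M, but the result would then contain nothing beyond mosquito density and infection. If f × L differs before and after treatment, the ranks can differ, and the stated data cannot show that they do. In neither case do the data support a separate claim about infectivity.

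**The case against.** The strongest reply is that this is a condensed article. An approved full protocol (Version 1.2) and standard operating procedures exist. The unused L3 abbreviation suggests that larval work may be described there. The inclusion criteria also mention volunteer mosquito collectors, which sits oddly with spray catches done by institute entomologists and may hint at another type of catch. Whether the cited assays are stage-specific cannot be seen from the article. All of this stands as doubt, and it lowers confidence. It does not remove the mismatch: the article does specify the catch, its hours, its schedule, the assay and the software, and these do not yield the index that it says will be tested.

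Three stronger readings are tempting, and the document does not support them.

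- *That none of the components is measured.* A spray catch can give an indirect indoor biting proxy. The firm gap is the infective proportion and the larval load.
- *That quarterly and then 6-monthly rounds make a monthly index impossible.* The plan promises a before/after comparison, not a continuous monthly series, and each sampled month could give a value. Unsampled months are not in themselves a defect.
- *That this index is the trial's measure of transmission intensity.* It is named once, is not among the primary or key secondary outcomes in Table 2, and stands beside a planned test of mosquito infection rates. The entomological objective does not depend on it alone.

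**Conclusion.** The point holds as an internal mismatch between a named test and the stated methods. As described, the collections and assays measure mosquito infection, with at best a proxy for indoor biting; they do not measure infectivity. The unobserved factor spans 50-fold under the assumed ranges, which are illustrative and not taken from the article.

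The conclusion rests on the usual three-factor definition of the index and on the article's methods being complete in this respect. Confidence is moderate, because the full protocol may contain L3 identification and counts or a further type of catch. The human primary outcome and the planned infection-rate comparison are unaffected. The correction is still worth making, because it is cheap and prevents an unsupported claim about transmission.

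**What to change.** Reconcile Entomologic surveillance, Data management and analysis, and Analysis strategy.

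- If the full protocol already provides L3 identification, L3 counts and a way to derive the biting rate, state these and define the index.
- If not, delete the monthly transmission potential test. Use the pool-screen estimate of *W. bancrofti* DNA prevalence by vector species, with confidence limits, compared between arms at each survey round. Comparing arms also agrees with the article's own rule that testing is confined to the two treatment groups, which a before/after test does not follow.
- Report indoor resting density beside it, and describe the result as mosquito infection, not as infectivity or transmission potential.

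The second route needs only a change of wording and no new collections, since the infection rate is already planned. Its cost is giving up a claim on transmission potential that the stated data do not support.
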